[figure not shown]

| Title                                   | PSMA-PET Guided Radiotherapy in Patients with High-Risk, Recurrent, or Oligometastatic Prostate Cancer (PERa GU 17.1)                                                                                                                                                                                                                                                                                                                                                                                                                                                                                                                                                     |
| Population                              | Patients with high-risk, recurrent, or oligometastatic prostate cancer planned for definitive radiotherapy.                                                                                                                                                                                                                                                                                                                                                                                                                                                                                                                                                               |
| Number of Experimental Subjects         | n=130                                                                                                                                                                                                                                                                                                                                                                                                                                                                                                                                                                                                                                                                     |
| Number of Sites                         | Two- CHUM, CSSSL,                                                                                                                                                                                                                                                                                                                                                                                                                                                                                                                                                                                                                                                         |
| Duration of Patient Study Participation | 5 years                                                                                                                                                                                                                                                                                                                                                                                                                                                                                                                                                                                                                                                                   |
| Objectives                              | 
Primary Objective
 
 
1. To determine if PSMA-PET/CT guided RT is superior to standard RT as measured by improved failure-free survival.
 
 
Secondary Objectives
 
 
2. To determine acute and delayed toxicities.
 
3. To determine the rates of biochemical, radiological, local, regional, and distant failures, and time to next therapy.
 
4. To measure prostate-cancer specific and overall survival.
 
5. To measure health-related quality of life.
 
6. To measure the detection yield of PSMA PET/CT imaging.
 
 |
| Primary Hypothesis                      | PSMA-PET/CT image-guided radiotherapy (IGRT) improves failure-free survival compared conventional IGRT in patients at high-risk of metastases.                                                                                                                                                                                                                                                                                                                                                                                                                                                                                                                            |
| Estimated Time to Complete Enrollment   | Patients will be enrolled over 3 years.                                                                                                                                                                                                                                                                                                                                                                                                                                                                                                                                                                                                                                   |

20

21

22

## 1.0 Introduction

Prostate cancer (PCa) is the most common non-skin malignancy and the third leading cause of cancer death in North American men.[1] The accurately mapped metastatic state is a necessary prerequisite to guiding treatment in practice and in clinical trials.[2, 3] Imaging biomarkers (BMs) can provide information on disease volume and distribution, prognosis, changes in biologic behavior, therapy-induced changes (both responders and non-responders), durations of response, emergence of treatment resistance, and the host reaction to the therapies. The impact of advanced imaging is expected to be heightened in the context of novel therapeutics as well as in image-guided therapies, such as radiotherapy and stereotactic ablative radiotherapy (SABR).

Of particular relevance to metastatic prostate cancer is the emergence of a promising imaging technique involving new prostate specific membrane antigen (PSMA) positron emission tomography (PET) tracers. This approach has demonstrated higher sensitivity in detecting metastases, prior to and during therapy, than current imaging standard of care (CT and bone scan), and is not widely clinically available outside of the research realm in North America.

Positron emission tomography / computer tomography (PET/CT) is a nuclear medicine diagnostic imaging procedure based on the measurement of positron emission from radiolabeled tracer molecules *in vivo*. PSMA is a homodimeric type II membrane metalloenzyme that functions as a glutamate carboxypeptidase/folate hydrolase and is overexpressed in PCa. PSMA is expressed in the vast majority of PCa tissue specimens and its degree of expression correlates with a number of important metrics of PCa tumor aggressiveness including Gleason score, propensity to metastasize and the development of castration resistance.[4]

[18F]DCFPyL is a promising high-sensitivity second generation PSMA-targeted urea-based PET probe. Studies employing second-generation PSMA PET/CT imaging in men with biochemical progression after definitive therapy suggest detection of metastases in over 60% of men imaged.[3] In fact, PSMA-based PET has so far proven to have higher sensitivity than any other modality for localization of the site of recurrence. Applications that show promise and require further investigation include the characterization and risk stratification of primary PCa, complete staging of metastatic PCa to allow for PSMA-targeted radiotherapy and improved identification of patients with oligometastatic disease. One of the main advantage of this new PET tracer is that it is labeled with Fluor-18 instead of Gallium-68, which is the most commonly used ligand

in other PSMA targeted probes. The radionuclide F-18 has several physical advantages compared to Ga-68, including lower energy and shorter positron range providing higher image resolution, longer half-life (110min vs. 68min) enabling multiple scans from a single formulation, and shipment to other sites without radiochemistry/cyclotron capability.

Here we hypothesize that definitive RT informed by PSMA-PET findings will lead to improved cancer control outcomes compared with RT guided by conventional staging only. We will utilize a cmRCT design, where eligible patients will be randomly selected for PSMA-PET/CT imaging prior to RT and approached for this investigational study. This study will therefore be conducted in companion to PERA (Partnership initiative for the Evaluation of technological innovation in Radiotherapy, CHUM CER 17.032).

## **2.0 Objectives**

### **2.1 Primary objective**

- 2.1.1 To determine if PSMA-PET/CT guided RT is superior to standard RT as measured by improved failure free survival.

### **2.2 Secondary objectives**

- 2.2.1 To determine acute and delayed toxicities.
- 2.2.2 To determine the rates of biochemical, radiological, local, regional, and distant failures, and time to next line therapy.
- 2.2.3 To measure prostate cancer specific and overall survival.
- 2.2.4 To measure health-related quality of life.
- 2.2.5 To measure the detection yield of PSMA PET/CT imaging.

## **3.0 Eligibility Assessments**

### **3.1 Inclusion criteria**

- 3.1.1 Enrolled in PERa registry (CHUM CER 17.032), consented to contact for investigational trials, consented to serve as control, and randomly selected to be offered the experimental intervention.

- 3.1.2 Histological diagnosis of prostate cancer planned for definitive-intent radiotherapy.
- 3.1.3 ECOG 0-1
- 3.1.4 Charlson Cormobidity Index  $\leq 4$
- 3.1.5 High-risk of distant metastases as defined by any of:
- 3.1.5.1 Oligometastases ( $\leq 5$ ) (regional or distant) identified on conventional staging, with  $\leq 3$  metastasis in any non-bone organ. For a spine metastasis, direct involvement of adjacent spinal segments would still be considered as “one” tumour. For nodal metastases, more than one involved lymph node in the same ipsilateral nodal region/chain would still count as “one” tumour. Defined nodal regions for this protocol include inguinal, external iliac, internal iliac, common iliac, retroperitoneal, hilar/mediastinal, anterior cervical, posterior cervical, and axillary. Metastases in all other organs that are within 1cm of each other will be considered as “one” tumour.
  - 3.1.5.2 Subjects with newly diagnosed high-risk (NCCN) localized prostate cancer and CAPRA score 6-10.
  - 3.1.5.3 Subjects with a prior history of treated prostate cancer
    - Post-radical prostatectomy and biochemical failure ( $> 0.1\text{ng/ml}$ )
    - Post-curative radiotherapy and biochemical failure (Phoenix-RT)

## 3.2 Exclusion Criteria

- 3.2.1 Prior androgen deprivation therapy terminated  $< 12$  months prior to enrollment.
- 3.2.2 Prior or planned PET scan.

## 4.0 Enrollment procedures

- 4.1 Confirmation of patient`s eligibility
- 4.2 Enrollment will occur after consent is completed.
- 4.3 Study Registration
- 4.3.1 Registration will occur only after pre-treatment evaluations and informed consent are completed.

## 6.0 Study Implementation

### 6.1 Study Design

6.1.1 Nested within the Partnership Initiative for the Evaluation of Technological Innovation in Radiotherapy (PERA - NCT03378856) prospective cohort, we will perform a Randomized Controlled Trial (RCT) comparing PSMA-guided radiotherapy (PSMAgRT) to controls.

When entering the PERA cohort, consent is asked for the use of data and for being approached for future research. Random selection of eligible patients to this trial were offered PSMAgRT. Outcomes will be compared with eligible patients randomized to a control arm and receiving usual care.

### 6.2 Procedures

6.2.1 PSMA -PET radiotracer provided by either: CRCHUM or PROGENICS Pharmaceuticals Inc. Use of this radiotracer in humans at the CHUM will be permitted following approval of this Positron-emitting Radiopharmaceutical for use in a CTA from Health Canada.

#### 6.2.2 PSMA -PET/CT scanning

6.2.2.1 To be performed within 4 weeks of registration (or when PSA > 0.1ng/ml for patient post RP)

6.2.2.2 [18F]-DCFPyL PET/CT studies will be performed on hybrid PET/CT scanners which combine a dedicated, full-ring PET scanner with a multi-slice spiral CT scanner. Patients should fast for at least 4 hours to facilitate transit of oral contrast into the distal small bowel. A volume of 200-400 ml of barium sulfate oral contrast can be administered and  $9 \pm 1$  mCi ( $333 \pm 37$  MBq, calculated and decay-corrected) of [18F]-DCFPyL is injected by slow intravenous push followed by saline flush. 90 minutes (+/- 30 minutes)

following [18F]-DCFPyL injection, CT and PET images are consecutively acquired from the base of the skull to mid-thighs. Additional images of the skull, lower extremities or upper extremities might be acquired if there is a clinical suspicion of lesion at these sites. Repeat imaging of equivocal foci can be obtained up to 180 minutes post-IV. Optionally, Lasix 10-40 mg IV may be administered 30-60 minutes prior to primary or repeat imaging to help clear urinary bladder activity.

6.2.2.3 For the CT scan portion of the study, the following are suggested, (slight variation based on clinical sites' clinical routine is acceptable): 120-140 kVp, 60–140 mA (depending on the body weight or noise index), a rotation time of 0.8 s, a pitch of 1.75:1, and a detector row configuration using 0.625 mm thick detectors. For the PET portion of the study, a 3D acquisition is performed and images are acquired using 2-5 min per bed position (depending on the body weight and PET detector crystal composition) and 5 to 6 bed positions are used (depending on the patient's height). Non-stop-motion PET is also acceptable if the PET scanner has this feature. Time-of-flight imaging is encouraged if the PET scanner has this feature. PET attenuation-corrected, PET non-attenuation-corrected, CT, and fused images are available for review in the transaxial, coronal, and sagittal planes with an ordered subset expectation maximization (OSEM) or similar iterative algorithm for the PET images.

6.2.2.4 The uptake of the lesions will be measured with SUVmax. SUVmax will be calculated using the usual formula with computations that also consider the post-injection residual activity. Patients will be weighed in the imaging department. Hepatic and blood pool SUV will be determined for the computation of tumor-to-liver and tumor-to-blood ratios.

6.2.2.5 Experienced central readers from each institution will adjudicate by consensus for each newly detected lesion beyond standard-care imaging. Disagreements between two experienced readers will be adjudicated by a tie-breaking third vote of a

195 separate nuclear medicine physician. Central review may result in  
 196 recommendation of MRI and/or biopsy of suspicious lesions.

197

198 6.2.2.6 Reports will be provided to treating physicians within 3  
 199 weeks of imaging.

200

201 6.2.2.7 Images will be provided if requested by treating physician  
 202 to assist in treatment planning.

203

204 6.1.3 Confirmation MRI: In cases where PSMA -PET/CT findings are  
 205 uncertain, an MRI of the questioned lesion site may be performed  
 206 at the discretion of the treating team.

207

208 6.1.4 Radiotherapy

209 6.1.4.1 PSMA -PET/CT imaging – no additional lesions detected: If  
 210 no additional lesions are detected, radiotherapy to  
 211 proceed as planned per standard care.

212 6.1.4.2 PSMA-PET/CT imaging – consistent with oligometastases  
 213 (1- 5 lesions): ALL oligometastatic lesions must be  
 214 treated with definitive radiotherapy. (see Guide –  
 215 Appendix 1)

216 6.1.4.3 PSMA-PET/CT imaging – consistent with widely metastatic  
 217 disease (>5 lesions): Treatment of all detected disease with  
 218 radiotherapy is not recommended. Physicians may alter  
 219 their radiotherapy plan as their discretion. However  
 220 treatment of the primary disease is encouraged.

221 6.1.4.4 RT summary to be provided (Impact of PSMA, Date  
 222 completed, Dose, Fractionation, Sites treated)

223

224 6.1.5 Hormonal therapy

225 6.1.5.1 At the discretion of the treating physician. However a  
 226 change in hormonal therapy is discouraged.

227

228 6.1.6 Follow-up

229 6.1.6.1 Per standard care practice / PERa, at least annually with  
 230 PSA and EPIC questionnaires.

231 6.1.6.2 Biochemical failures (Phoenix) to be investigated per  
232 standard care.

233 6.2 Withdrawal Criteria

234 Patients may be taken off study prior to the completion of study related  
235 procedures for the following reasons:

236 6.2.1 Patient withdraws consent for participation.

237 6.2.2 It is deemed in the patient's best interest as determined by the  
238 attending/PI.

239 6.2.3 Serious protocol violation as determined by the PI

240 6.2.4 Development of a concurrent serious medical condition during the  
241 studies or treatments precluding completion of study procedures.

242 6.2.4 Completion of per-study follow-up (5 years after radiotherapy)

243 **7.0 Data collection and Confidentiality**

244 7.1. Hard Copies

245 6.1.1.1 Consent forms

246 7.2 Electronic Data

247 7.2.1 Medical records (Eg. EMR, OACIS, MOSAIC)

248 7.2.2 Imaging Data (Eg. Clinical PACS, Research PACS), including  
249 anonymized electronic submission for the research access use of 18F-  
250 DCFPyL imaging.

251 7.2.3 Research Data (Eg. Excel spreadsheet, Research PACS, Nuclear  
252 Medicine Reports, CASTOR EDC)

253 7.3 Confidentiality

254 7.3.1 In all research records, subjects will be identified by enrollment  
255 number.

256 7.3.2 Research data will be under secure password, or kept under lock  
257 and key in the research office.

258 7.3.3 No records bearing patients identification will be provided to  
 259 anyone outside of the institution except regulatory agencies.

260 7.3.4 Patients will not be identifiable as individuals in any publication or  
 261 presentation that may result from this study.

262 7.4 Data Safety and monitoring plan

263 7.4.1 PI will assume primary responsibility for monitoring the progress  
 264 of the trial and the safety of participants.

265 7.4.2 Data will be submitted to the REC annually for continuing review  
 266 and at the completion of the study per institutional guidelines.

267 **8.0 Study Endpoints**

268 8.1 Failure-free survival, defined as time to biochemical failure (Phoenix  
 269 definition, Roach 2006, or >0.2ng/ml for post-RP strata), local failure, regional  
 270 failure, distant metastases, initiation of the next line of therapy, or death  
 271 from any cause. (measured from end of RT) Event-free patients are  
 272 censored at their last known follow-up date.

273 8.2 CTCAE v5.0: Attributable Gr2+ toxicities.

274 8.3 Rates of biochemical failure, local failure, regional failure, distant failure, and  
 275 radiological failure.

276 8.4 Disease specific and overall survival

277 8.5 Health related quality of life: EPIC-CP, FACT-P, IPSS

278 8.6 Detection yield of PSMA-PET

279 **9.0 Human subjects protection**

280 9.1 Evaluation of Risks/Discomforts

281

282 9.1.1 Risk of PSMA -PET/CT imaging: There is extensive clinical  
 283 experience using F-labeled radiotracers, especially  
 284 fludeoxyglucose (FDG). This experience has demonstrated the  
 285 safety of PET imaging, which is now used routinely for diagnostic,  
 286 radiation treatment planning and research purposes worldwide.  
 287 There are no risks related to the PET imaging acquisition itself,  
 288 potential risks are probe-specific.

289 Radiopharmaceuticals are generally not associated with side  
 290 effects. Allergic reactions are excessively rare. Pharmacokinetic

and dosimetric characterization of PSMA-PET has been previously performed in humans. Rapid and nearly static biodistribution after 20-30 minutes has been observed for [F]DCFPyL, with negligible blood/serum/RBC activity measured 25 minutes after injection . The effective (whole body) dose for 370MBq (10mCi) [F]DCFPyL injection is approximately 0.0165 mSv/MBq. This dose is below the 0.03mSv/MBq upper limit recommendation by the FDA for diagnostic tests, and corresponds roughly to 2.5 additional years of background exposure. The dose-critical organs doses are: kidneys (0.0896 mGy/MBq), bladder wall (0.0873 mGy/MBq), submandibular glands (0.0418 mGy/MBq), and liver (0.0420 mGy/MBq). Preliminary studies have showed high rates of uptake in tumours of patients with prostate and renal cancer, and increased performance compared to other PSMA-targeted probes. No documented serious adverse events (SAE) considered related to 18F-DCFPyL have been recorded in the trials using [F]DCFPyL, and its use has been previously approved for investigational purposes by Health Canada.

During PSMA -PET/CT scanning, patients are exposed to a small dose of radiation (10-12mSv). This dose is not associated with any risk in the context of patients receiving radiotherapy.

9.1.2 Risk of IV injection: Use of imaging contrast/probe agents during intravenous injection will involve minimal discomfort to the patient and can occasionally result in mild soreness or bruising. This may rarely lead to superficial thrombophlebitis in less than 5% of patients.

9.1.3 Risk of radiation toxicity: Radiation treatment to oligometastatic sites identified on PSMA -PET/CT may lead to side-effects. Dose objective and normal tissue exposure constraints will respect standard care practice; therefore the risks are equivalent to standard-care definitive radiotherapy to those sites.

Acute side effects are expected to be low (<10%), they include fatigue, skin reactions, and side-effects specific to the areas being treated. In rare instances, exposure to high doses of radiotherapy may result in late severe adverse effects such as: myelitis,

neurological deficits, proctitis, bowel symptoms and/or perforation. Nonetheless, considering the expected low burden (and volumes) of disease to be treated, the study has been designed to respect standard-care dose-volume limits to organs at risk, while maintaining a definitive dose to the tumor. In this manner, the risk of severe late adverse events is expected to be very low (<5%).

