## 385 386 10.0 ETHICS

387  
388 10.1 The study will be submitted for initial and ongoing annual REB review.  
389 Study related procedures will not commence prior to receipt of REB approval.

390  
391 10.2 Any amendment to the study will be submitted for review by the REB  
392 before any changes are implemented unless required to eliminate immediate  
393 hazard to the study participants.

394  
395 10.3 Data derived from this study may be reported in scientific publications.  
396 Patients will not be indicated by name.

397  
398 10.4 Sample size determination

399 This study will employ a cmRCT design to determine the potential benefit of  
400 PSMA-PET guided radiotherapy in patient with high-risk of micro/oligo

metastatic disease. Patients will be randomly selected (1:1) for this intervention from the PERA study if they provide consent and meet eligibility criteria. The study will be designed with an  $\alpha=0.1$  and 80% power (as recommended for phase II randomized trials) for the primary outcomes. Patients will be stratified according to institution and category at time of enrollment (oligometastatic - estimated 15% of cohort) vs. high-risk localized – estimated 35% of cohort, vs. recurrent post RT – estimated 5% of cohort vs. recurrent post RP – estimated 45% of cohort).

Literature suggests that PSMA PET/CT can increase the diagnostic yield (sensitivity) for bone metastases by 10-15% compared with standard staging (approximately 85% to 99%), and for lymph node metastases by 50% (25% to 75%), resulting in over 60% of patient with high-risk of metastases demonstrating new identifiable lesions on PSMA PET. Adjusting for the proportion surviving free of failure at 5 years within the strata (0.05, 0.6, 0.3, and 0.4, respectively), a total of 130 patients receiving a PSMA -PET/CT evaluation (and 130 control) will be required to demonstrate benefit over standard care ( $\alpha=0.1$ ,  $\beta=0.8$ , one-tailed, HR 1.4).

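### The stated 80% power needs about 159–160 events, but ending follow-up 5 years after radiotherapy gives about 139 events and about 76% power if the stated 5-year proportions are control-arm rates.

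*Protocol*

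**What the plan says.** Protocol section 10.4 claims "80% power (as recommended for phase II randomized trials" with alpha 0.1, and later in the same section specifies "one-tailed, HR 1.4". Allocation is 1:1, and the sample size is "a total of 130 patients receiving a PSMA -PET/CT evaluation (and 130 control" patients. The strata are oligometastatic 15%, high-risk localized 35%, recurrent after radiotherapy 5% and recurrent after prostatectomy 45%. Their 5-year failure-free proportions are 0.05, 0.6, 0.3 and 0.4. The section does not say which arm these proportions describe. It gives no required number of events and no allowance for loss.

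On duration, the synopsis states "Patients will be enrolled over 3 years" and sets patient participation at 5 years. The last item of the withdrawal criteria (section 6.2) is "Completion of per-study follow-up (5 years after radiotherapy". Section 8.1 measures FFS from end of radiotherapy and censors event-free patients at last known follow-up.

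Section 10.4 also sets beta to 0.8 beside the power of 80%, and gives a hazard ratio above 1 for a benefit without stating its direction.

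**The concern.** The power of a log-rank comparison depends on the number of events, and that number depends on how long patients are followed. The 5-year stop and the FFS clock both start from radiotherapy, so the stop cuts the endpoint at the very time to which the stated failure-free proportions refer. The expected events can therefore be read almost directly from section 10.4, and on the natural reading they fall short of what 80% power requires. At stake is a stated property of the primary analysis: a chance of missing a true hazard ratio of 1.4 of about 24% rather than 20%. Events that occur after early patients leave the study may not be recoverable if nothing provides for collecting them.

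**Working it through.** **Inputs.** From section 10.4: one-sided alpha 0.1 (z = 1.2816), power 80% (z = 0.8416), hazard ratio 1.4 read as control:PSMA, 130 per arm, stratum shares w = 0.15, 0.35, 0.05, 0.45, and 5-year proportions S = 0.05, 0.6, 0.3, 0.4. From the synopsis: 3 years' accrual. From section 6.2 and the synopsis: 5 years per patient.

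**Step 1: events needed (Schoenfeld, 1:1).**
4 × (1.2816 + 0.8416)² / (ln 1.4)² = 159.3, that is 159–160 events. Freedman's formula gives 163.

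**Step 2: can the stated sample size be reproduced?** Take S as control rates, exponential failure within stratum, uniform accrual over 3 years, and follow every patient to 5 years after the last patient starts the FFS clock (5 to 8 years each). Expected events are 86.6 control + 73.0 PSMA = 159.7 after rounding, and power is 80.1%. So 130 + 130 is consistent with 5 to 8 years of follow-up.

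**Step 3: events with a 5-year stop, S as control rates.**
- Control: 1 − (0.15×0.05 + 0.35×0.6 + 0.05×0.3 + 0.45×0.4) = 1 − 0.4125 = 0.5875, giving 130 × 0.5875 = 76.4 events.
- PSMA: S^(1/1.4) = 0.1177, 0.6943, 0.4232, 0.5197 by stratum. The weighted mean is 0.5157, so the event probability is 0.4843, giving 130 × 0.4843 = 63.0 events.
- Total: 130 × (0.5875 + 0.4843) = 139.3 events.
- Power = Φ(√139.3 / 2 × ln 1.4 − 1.2816) = 75.9%.

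The event count in this step needs only proportional hazards within strata, with no assumption about accrual or the shape of the survival curve. Freedman's approximation gives 75.4%, and a simulated stratified log-rank test gave 74.7%.

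**Step 4: other readings of S, same 5-year stop.**

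| Reading of the 5-year proportions | Events | Power |
|---|---|---|
| Control arm | 139.3 | 75.9% |
| Same rates in both arms when counting events | 260 × 0.5875 = 152.8 | 78.7% |
| Experimental arm | 166.4 | 81.3% |

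**Step 5: what would restore 80% under the 5-year stop (control-rate reading).** About 159 / (139.3/260) = 297 patients at hazard ratio 1.4. With 260 patients, power reaches 80% at a hazard ratio of about 1.435 (138.4 events, 80.0%).

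**Step 6: loss and the start of the clock.** Both figures here are assumptions that the protocol does not give. With 2% loss per year, the 5-year stop gives 133.8 events and 74.7%, and the 5-to-8-year follow-up gives 151.8 events and 78.6%. If a common cut-off is counted from randomisation rather than end of radiotherapy, with a 6-month lag between the two, follow-up is 4.5 to 7.5 years, giving 153.1 events and 78.8% without loss.

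**The case against.** The strongest objection is that the 5-year stop may not be firm. The withdrawal list is permissive: it says what may happen, not what must. The follow-up section (6.1.6) refers to standard care and the PERa registry and sets no end, and section 8.1 censors at last known follow-up rather than at 5 years. Registry data beyond 5 years might therefore enter the analysis, and the timing of the final analysis is something a statistical analysis plan commonly settles. This stands in part: the documents do not prove that later events will be discarded. But the synopsis independently sets participation at 5 years, the withdrawal item treats that point as completion of study follow-up, and no passage plans later collection of the primary endpoint. The stated power should not depend on follow-up that the protocol does not provide for.

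The second objection is that section 10.4 never calls the proportions control-arm rates. This also stands. A reader might infer that the sample size can be reproduced only with follow-up beyond 5 years, or that 76% is the one figure the protocol implies. The documents support neither: the experimental-arm reading reaches 81.3% within 5 years, and equal rates in both arms give 78.7%. The control-arm reading is the natural one because the proportions are used to size a benefit over standard care, but it remains a reading.

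Third, about 4 points is modest in a phase II trial at one-sided alpha 0.1. It biases no estimate and leaves the type I error rate unchanged. That limits the weight of the point but does not make the passages consistent.

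**Conclusion.** The point holds as an inconsistency of moderate size and is a should-fix. Eighty percent power needs about 159–160 events. With follow-up ending 5 years after radiotherapy and the stated proportions read as control-arm rates, the design yields about 139 events and about 76% power, some 20 events and 4 points short, before any loss. Across the possible readings the range is about 76% to 81%. The match at 5 to 8 years of follow-up suggests that the sample size was derived that way, but does not prove it.

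The conclusion rests on three assumptions: the 5-year stop applies to the FFS endpoint, the proportions are control-arm rates, and hazards are proportional within strata. A reader might go further and conclude that the trial is seriously underpowered or its primary analysis invalid. Neither follows from a 4-point shortfall that one sentence on follow-up could remove or disclose. The beta of 0.8 is an evident slip, since the power is stated correctly in the same section, and the unlabelled hazard ratio can be understood from context. Both are minor.

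**What to change.** Reconcile section 10.4 with the synopsis and section 6.2 in one of two ways.

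(a) Keep the 5-year stop. State that the 5-year proportions are control-arm rates, and restate power as about 76% at hazard ratio 1.4, or 80% at about 1.435, both before loss to follow-up. The cost is a less favourable stated power.

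(b) State that FFS follow-up continues through PERa for all patients in both arms. Set one trigger for the final analysis: either about 160 events, or a common cut-off 5 years after the last patient's end of radiotherapy with power quoted net of expected loss. Do not combine the two, because they need not coincide, and do not count the cut-off from randomisation, because the FFS clock starts later. The cost is an amendment reviewed by the research ethics board, possibly a consent update because the participation period changes, and up to 3 more years of routine registry follow-up for early patients. No new patients are needed.

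In either case, correct beta to 0.2 and label the hazard ratio as control:PSMA 1.4 (PSMA:control 1/1.4 = 0.71).
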